## Abstract

**Introduction:**

Antimicrobial resistance undermines our ability to treat bacterial infections, leading to longer hospital stays, increased morbidity and mortality, and a mounting burden to the healthcare system. Antimicrobial stewardship is increasingly important to safeguard the efficacy of existing drugs, as few new drugs are in the developmental pipeline. While significant progress has been made with respect to stewardship in hospitals, relatively little progress has been made in the primary care setting, where the majority of antimicrobials are prescribed. OPEN Stewardship is an international collaboration to develop an automated feedback platform to improve responsible antimicrobial prescribing among primary care physicians and capable of being deployed across heterogeneous healthcare settings. We describe the protocol for an evaluation of this automated feedback intervention with two main objectives: assessing changes in antimicrobial prescribing among participating physicians and determining the usability and usefulness of the reports.

**Methods and analysis:**

A non-randomised evaluation of the automated feedback intervention (OPEN Stewardship) will be conducted among approximately 150 primary care physicians recruited from Ontario, Canada and Southern Israel, based on a series of targeted stewardship messages sent using the platform. Using a controlled interrupted time-series analysis and multilevel negative binomial modelling, we will compare the antimicrobial prescribing rates of participants before and after the intervention, and also to the prescribing rates of non-participants (from the same healthcare network) during the same period. We will examine outcomes targeted by the stewardship messages, including prescribing for antimicrobials with duration longer than 7 days and prescribing for indications where antimicrobials are typically unnecessary. Participants will also complete a series of surveys to determine the usability and usefulness of the stewardship reports.

**Ethics and dissemination:**

All sites have obtained ethics committee approval to recruit providers and access anonymised prescribing data. Dissemination will occur through open-access publication, stakeholder networks and national/international meetings.

Strengths and limitations of this studyMultinational pragmatic study.Large number of providers studied with extended follow-up.Comprehensive evaluation including pre–post design and concurrent controls.Scalable and open concept with potential for broad generalisability to various care settings.Differences in recruitment strategy for intervention group across the two study sites may result in heterogeneity of intervention effect.

## Introduction

The WHO has called antimicrobial resistance ‘one of the biggest threats to global health, food security and development today’.^1^ Antimicrobial resistance undermines our ability to treat bacterial infections, leading to longer hospital stays, increased complications, higher mortality and a mounting resource burden on healthcare systems globally.^1–5^ It has been projected that resistant microbes could contribute to up to 10 million deaths per year by 2050, greater than the current annual burden of cancer deaths. Additionally, a cumulative loss in global production of trillions of US dollars in the same time frame is possible,^6^ hindering efforts to eliminate poverty.^7^ Despite a widespread recognition of antimicrobial use as the leading driver of resistance, inappropriate prescribing remains common.^8–10^ Given the paucity of new antimicrobials in the drug development pipeline,^11^ it is critical that we act to safeguard the effectiveness of existing drugs by reducing inappropriate antimicrobial prescribing.

Antimicrobial stewardship refers to the effort to promote the responsible use of antimicrobials and to ensure that patients receive the best choice, duration and route of antimicrobial treatment, while minimising potential side effects and the dissemination of antimicrobial resistance.^12^ While progress has been made in advancing antimicrobial stewardship in hospitals, leading to significant cost savings and improved patient outcomes,^13 14^ progress in the primary care setting has been slower.^15–17^ This is troubling, given that most antimicrobials are prescribed in the outpatient setting, rather than in hospitals (eg, over 90% in Canada).^18 19^ Supporting general and family practitioners with prescribing is especially important, since they account for the majority of antimicrobials dispensed for human use in Canada.^19^ The US Centers for Disease Control and Prevention have issued a checklist identifying the key elements to a successful antimicrobial stewardship programme in an outpatient setting, highlighting easy access to evidence-based prescribing guidelines and the technical capacity to track, evaluate and report on antimicrobial prescribing.^20^ An online, automated feedback system facilitating these elements would be a major asset to advancing stewardship in primary care.

OPEN Stewardship is an international collaboration with the goal of developing an open, web-based platform to improve antimicrobial prescribing among primary care physicians. This platform integrates with local antimicrobial prescribing data to provide participating physicians with regular, automated feedback (identified by a recent Cochrane review as an effective technique to enable appropriate antimicrobial prescribing in the hospital setting^14^) and connects users with locally relevant prescribing guidelines. The development of a standardised, accessible stewardship platform addresses a key gap for stewardship interventions in the primary care setting, namely the difficulty of expanding across heterogeneous, resource-constrained healthcare systems. As part of a One Health approach recognising the interconnectedness of human and animal health,^21^ the platform is also being developed for use in veterinary care, a sector where antimicrobial stewardship has received less attention.^22^ A study parallel to the present study will be occurring among veterinary care providers.

## Study approach and objectives

In this study, we will enrol primary care physicians on a voluntary basis from practices in two study sites: Ontario, Canada and Southern Israel. Non-participating physicians (from the same healthcare network) will be available as controls. The intervention group will receive three personalised electronic reports sent over the span of 6 months, benchmarking their prescribing rate to those of their peers and attaching locally relevant prescribing guidelines for specific indications. The messaging will target antimicrobial prescribing longer than 7 days (few conditions require longer than this^23^), as well as two indications in particular: acute sinusitis and viral respiratory conditions. These common infections are a promising target for stewardship.^8 20 24 25^ In the USA, acute respiratory conditions as a whole account for close to half of antimicrobials prescribed and a great majority of those prescribed inappropriately in the ambulatory care setting.^8^

The aim of this project is to assess the impact of an automated feedback intervention on antimicrobial prescribing in primary care physicians. Specifically, for a cohort of primary care physicians in Ontario, Canada and Southern Israel, we will determine the impact of the stewardship intervention on:

The overall antimicrobial prescribing rate in the period following the intervention compared with the period preceding it and to a cohort of primary care physicians who did not receive the intervention.The prescribing rate for antimicrobials with duration longer than 7 days in the period following the intervention compared with the period preceding it and to a cohort of primary care physicians who did not receive the intervention.The antimicrobial prescribing rate for viral respiratory conditions in the period following the intervention compared with the period preceding it and to a cohort of primary care physicians who did not receive the intervention.The antimicrobial prescribing rate for acute sinusitis in the period following the intervention compared with the period preceding it and to a cohort of primary care physicians who did not receive the intervention.

We will also assess:

The usability and usefulness of each component of the antimicrobial stewardship reports, as well as the usefulness of the reports overall.

## Methods and analysis

### Objectives 1–4: non-randomised evaluation of intervention with interrupted time-series analysis.

#### Study design

Primary care physicians (providers) from two study sites will be voluntarily enrolled to participate in an antimicrobial stewardship intervention. The providers’ rates of antimicrobial prescribing after the intervention will be compared with their rates prior to having received the reports, as well as the prescribing rates of their peers in the same network who did not participate in the intervention. This study design is know as a controlled interrupted time-series.^26^ Our study design addresses the limitations of some previous studies of stewardship interventions, including small sample sizes, single-centre design, a lack of external controls and short follow-up.^16^

#### Participants

Approximately 100–150 general practitioners will be enrolled from two study sites: Ontario, Canada (50) and Southern Israel (50–100). Participants will be drawn from the University of Toronto Practice-Based Research Network (UTOPIAN) and Clalit Health Services (CHS), respectively. UTOPIAN is ‘one of the largest and most representative primary care research networks in North America’,^27^ including data for over 400 physicians with an average practice size of 1018 patients.^28^ This includes family medicine practices and primary care practices in university-affiliated hospitals. CHS is the largest healthcare maintenance organisation in Southern Israel^29^ and covers nearly 80% of the population in Southern Israel through a network family medicine practices. Existing data storage and sharing facilities within both of these networks allow access to de-identified patient data for research in the primary care setting.

In Ontario, primary care physicians will be voluntarily enrolled, provided they worked for at least 12 months prior to the intervention, expect to continue working for the 12 months following the start of the intervention and are not actively participating in another stewardship intervention. Providers will be approached for enrolment via email or in-person presentations to groups of providers. Participants will begin the intervention in at least two waves in different months. In Southern Israel, half of the approximately 400 eligible physicians (average number of patients: 1482) will be randomised (using random assignment in an Excel spreadsheet by the study coordinator) to be approached (via a letter from the chief physician, followed by contact by an interviewer) for voluntary enrolment in the study. Anonymised prescribing data of non-participating physicians within UTOPIAN and CHS will be available as an external control group (approximately 350 for UTOPIAN and 250–300 for CHS, with an expected 25%–50% response rate for physicians approached to enrol).

It is possible that physicians who voluntarily enrol in the antimicrobial stewardship intervention will be more engaged with stewardship prior to the intervention, and thus may have less to gain from a stewardship intervention than less-engaged physicians. Differences in the recruitment strategy between sites may result in a heterogeneity in the observed effect, which will be accounted for in the analysis.

#### Intervention

The intervention will consist of three personalised reports generated by the OPEN Stewardship platform and emailed to participants in the intervention group. The first report will be sent at the beginning of the intervention period (*t_0_*) and will consist of a welcome email followed by a benchmark of the provider’s overall antimicrobial prescribing rate relative to the average and 25th percentile of participants in the same network (UTOPIAN or CHS) during the previous year (2019). This report will also include guidelines highlighting that most conditions do not require more than 7 days of antimicrobials and a benchmark of the provider’s proportion of antimicrobial prescriptions with duration longer than 7 days relative to the average and 25th percentile of participants in the same network during the previous year. We chose to benchmark against other participants only (excluding non-participants) due to the expectation that those self-selecting into a stewardship intervention may already have lower rates of prescribing.

The two subsequent reports will be sent 3 (*t_3_*) and 6 (*t_6_*) months after the first report. These reports will target viral respiratory conditions (as defined by the primary International Classification of Diseases, Ninth Revision (ICD-9) code associated with the visit, see online supplemental table S1) and acute sinusitis, respectively, and will consist of a benchmark of the provider’s prescribing for the specified indication as well as site-specific best practice guidelines for the specified indication. The study concludes 1 year after the first report is sent (*t_12_*). The composition of each report is summarised in table 1. An example figure is shown in figure 1.

10.1136/bmjopen-2020-039810.supp1Supplementary data

**Figure 1 F1:**
[figure not shown]
Example of chart sent in the first feedback report, representing the provider’s prescribing rate/100 visits for any indication versus the average rate and 25th percentile rate across all providers in the study from the same study site.

**Table 1 T1:** Composition of the feedback reports (intervention) at each time point

Feedback report	Content of report	Benchmarking figure	Guidelines
Report at *t_0_*	1. Antimicrobial prescribing rate/100 visits in the previous year for all visits. 2. Proportion of antimicrobial prescriptions in the previous year with duration over 7 days.	Provider’s own rate/proportion versus average rate/proportion and 25th percentile rate/proportion across all participants at the same study site.	Guidelines indicating that antimicrobial prescribing longer than 7 days is not necessary for many conditions.
Report at *t_3_*	1. Antimicrobial prescribing rate/100 visits in the previous year for viral respiratory conditions.	Provider’s own rate versus average rate and 25th percentile rate across all participants at the same study site.	Prescribing guidelines for viral respiratory conditions.
Report at *t_6_*	1. Antimicrobial prescribing rate/100 visits in the previous year for acute sinusitis.	Provider’s own rate versus average rate and 25th percentile rate across all participants at the same study site.	Prescribing guidelines for acute sinusitis.

#### Outcomes

Each of the four objectives corresponds to an outcome, measured for each provider as the monthly prescribing rate per 100 visits for a particular indication. This prescribing rate is calculated as the number of prescriptions for a particular indication divided by the number of patient visits for that indication in a month, multiplied by 100.

Overall prescribing rate for antimicrobials.The prescribing rate for antimicrobials lasting longer than 7 days in duration.The prescribing rate for visits classified as being for a viral respiratory condition (see online supplemental table S1 for ICD-9 codes).The prescribing rate for acute sinusitis visits.

While overall antimicrobial prescribing is a proxy for our desired measure, which is appropriate antimicrobial prescribing, the microbiological data do not exist to validate the appropriateness of each individual prescription. Nonetheless, given the ubiquity of inappropriate prescribing, particularly for acute respiratory tract infections, any reduction in prescribing as a result of the intervention is likely to be positive.^8 30 31^

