#### Covariates

The analysis will include potential predictors of a provider’s baseline prescribing rate, as well as seasonality (table 2). These include a provider’s age, sex and employment status (full-time or part-time),^10^ and monthly practice patient composition (by age and sex).^19 32^ We will also use nested random intercepts for provider, practice group (clinic) and study site, representing within-group prescribing norms and a provider’s baseline willingness to prescribe after accounting for other predictors, as well as heterogeneity between study sites. Seasonality will be accounted for using a categorical variable for each month compared with January. An interaction term with study site will be included for each covariate to allow for differences in seasonal and demographic prescribing patterns between the two countries in our study.

**Table 2 T2:** Covariates included in the interrupted time-series analysis of the OPEN Stewardship Study

Variable	Purpose	Form	Description
Number of prescriptions	Outcome	Integer	Number of antimicrobial prescriptions for given indication
Number of visits for indication	Offset	Integer	Number of patient visits for given indication
Study site	Covariate	Binary	Southern Israel versus Ontario, Canada (baseline)
Practice group	Random intercept	ID	Random intercept for practice group (nested within region)
Provider	Random intercept	ID	Random intercept for provider (nested within practice group)
Month	Covariate	Categorical	Calendar month (baseline=January)
Month×study site	Interaction	Interaction	Allows different value for coefficients for Southern Israel
Physician age	Covariate	Integer	Physician age at *t_−12_*
Physician age×study site	Interaction	Interaction	Allows different value for coefficient for Southern Israel
Physician sex	Covariate	Binary	Female versus male (baseline)
Physician sex×study site	Interaction	Interaction	Allows different value for coefficient for Southern Israel
Physician employment status	Covariate	Binary	Part-time versus full-time (baseline)
Physician employment status×study site	Interaction	Interaction	Allows different value for coefficient for Southern Israel
Percent female patients	Covariate	Continuous	Percentage of visits by female patients
Percent female patients×study site	Interaction	Interaction	Allows different value for coefficient for Southern Israel
Percent patients 17 and under	Covariate	Continuous	Percentage of visits by patients 17 and younger

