#### Sensitivity analyses

Alternative parameterisations of the study outcomes will be considered. For the prescribing rate of antimicrobials with courses longer than 7 days (objective 2), we will consider total days of therapy (with the number of prescriptions as the offset) as an alternative outcome using a zero-truncated negative binomial model. There may be issues with how indications are coded in the electronic medical record, whereas the type of antimicrobial prescribed is very likely to be accurate. A sensitivity analysis will be performed using the prescribing rates (for all visits) for antimicrobials most often prescribed for viral respiratory conditions (eg, amoxicillin, amoxicillin/clavulanic acid, azithromycin^37^) as the outcome, rather than the indication-specific prescribing rate of antimicrobials for viral respiratory conditions. Since acute respiratory tract infections make up a large proportion of total antimicrobial prescribing, the signal from the intervention may be evident using these outcomes as well.

To ascertain whether there could be negative effects of the stewardship intervention, we will evaluate (1) the frequency of bacterial pneumonia and pyelonephritis diagnoses and (2) the number of hospital admissions (including those related to infection) in the pre-intervention and post-intervention periods. Admissions data are only available for CHS (Israel), and thus will only be evaluated at this site only.

Including patient composition as predictors (eg, percentage of patients 65 and older, percentage of female patients) may be insufficient to capture differences in prescribing occurring between strata of age and sex. A sensitivity analysis will be performed where the outcome will be stratified by age group and sex and modelled separately. Although stratification increases the noise in each individual time-series, these models may reveal differences in the effectiveness of the intervention across sex/age groups, which have different prescribing patterns.

As the offer to enrol in the study is randomised at one study site (Southern Israel), an intention-to-treat analysis will be performed as a supplementary analysis at this site only. The characteristics and prescribing patterns of responders and non-responders among those offered enrolment will also be compared.

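### A feedback-induced shift in diagnosis coding would lower the objective 3 and 4 rates with prescribing unchanged, and the planned code-independent check is named for viral respiratory conditions but not for acute sinusitis

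*Protocol article*

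**What the plan says.** All references are to the protocol article.

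- **Outcome.** Under Outcomes: "This prescribing rate is calculated as the number of prescriptions for a particular indication divided by the number of patient visits for that indication", by month and per 100. Table 2 (Covariates) gives the model offset as "Number of patient visits for given indication".
- **How a visit is classified.** Under Intervention, viral respiratory conditions are "as defined by the primary International Classification of Diseases, Ninth Revision (ICD-9) code associated with the visit", with the code list in supplemental table S1, which is not shown. Outcome 4 is the rate for acute sinusitis visits.
- **What participants see.** Table 1 lists, for the t3 report, "Antimicrobial prescribing rate/100 visits in the previous year for viral respiratory conditions", and for the t6 report, "Antimicrobial prescribing rate/100 visits in the previous year for acute sinusitis". Each is set against the participant average and 25th percentile and comes with guidelines for that condition.
- **Timing.** Table 3 places the intervention at t0 for objectives 1 and 2, t3 for objective 3 and t6 for objective 4.
- **Recognition of coding problems.** Under Sensitivity analyses: "There may be issues with how indications are coded in the electronic medical record, whereas the type of antimicrobial prescribed is very likely to be" (the sentence ends by treating drug type as the reliable record). The response is: "A sensitivity analysis will be performed using the prescribing rates (for all visits) for antimicrobials most often prescribed for viral respiratory conditions", used "rather than the indication-specific prescribing rate of antimicrobials for viral respiratory conditions". Acute sinusitis is not mentioned there. The only diagnosis frequencies to be examined are bacterial pneumonia and pyelonephritis, as a check for harm.

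**The concern.** The t3 and t6 reports act on the label that defines the outcome. A participant who has been told that a diagnosis seldom warrants an antimicrobial may prescribe less for it. The same participant may instead come to record treated visits under a neighbouring diagnosis. No deliberate gaming is needed: guidance on what a label implies can change how the label is used. Either response lowers the indication-specific rate, and the rate alone cannot tell them apart.

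The control series does not help here. It removes changes shared by both groups, whereas a shift prompted by the reports would occur among participants only.

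At stake is the reading of objectives 3 and 4. A change of labels could be reported as a stewardship effect. If some visits moved to bacterial pneumonia, the harm check could show a rise that is also only a change of label.

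**Working it through.** **The plan's own figure.** The Sample size section takes a baseline of 0.126 prescriptions per visit and calls a 15% reduction clinically meaningful: 0.126 × 0.85 = 0.107, as stated. That figure concerns the all-visit rate. The article gives no indication-specific rate, so every baseline below is an assumption and 15% serves only as a yardstick.

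**Step 1: effect of recoding on the ratio.** Take 100 visits coded to the target, a rate r per visit and at most one prescription per visit. Let x treated visits move to a code outside the target, with no prescription withheld.

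- New rate = (100r − x)/(100 − x), which is below r for every r < 1 and x > 0.
- Example with r = 0.30 and x = 6: 24/94 = 0.255. The fall is 1 − 0.255/0.30 = 14.9%.

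**Step 2: number of visits that mimics a 15% fall.** Set (100r − x)/(100 − x) = 0.85r. Then x = 15r/(1 − 0.85r). As a share of treated visits this is 0.15/(1 − 0.85r).

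| Assumed rate per 100 | x per 100 coded visits | Share of treated visits |
|---|---|---|
| 20 | 3/0.830 = 3.6 | 18% |
| 30 | 4.5/0.745 = 6.0 | 20% |
| 40 | 6/0.660 = 9.1 | 23% |
| 50 | 7.5/0.575 = 13.0 | 26% |
| 70 | 10.5/0.405 = 25.9 | 37% |
| 80 | 12/0.320 = 37.5 | 47% |

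The artefact is easier to produce when the baseline rate is low. If untreated visits moved in the same proportion as treated ones, the rate would not change, so the table describes a shift confined to treated visits.

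**Step 3: can objective 1 stand in for a sinusitis check?** Recoding leaves the all-visit rate unchanged, so objective 1 is immune to it. Its usefulness depends on whether a true sinusitis effect would be visible there. Let s be the share of all visits that are for sinusitis. A true 15% cut in sinusitis prescribing changes the all-visit rate by s × r × 0.15/0.126.

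- s = 1%, r = 0.5: 0.01 × 0.5 × 0.15/0.126 = 0.6%.
- s = 5%, r = 0.8: 0.05 × 0.8 × 0.15/0.126 = 4.8%.

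Both s and r are assumed. Over that range a real cut and pure relabelling differ by only 0.6% to 4.8% on objective 1, whose intervention point is t0 rather than t6.

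**Step 4: coverage of the planned checks.**

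| Check | Immune to recoding | Viral respiratory | Acute sinusitis |
|---|---|---|---|
| Objective 1, all visits | Yes | Indirect, at t0 | Indirect, diluted, at t0 |
| Drug-based rate, all visits | Yes | Named for this outcome | Indirect; not named, not tied to t6 |
| Pneumonia count | No | Shows a shift into that one diagnosis | Same |
| Visit counts for the target diagnoses | – | Not described | Not described |

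**The case against.** The strongest reply is that the authors saw the coding problem and answered it. Objective 3 has a drug-based analysis that ignores the diagnosis. Its all-visit denominator dilutes the signal, but that denominator is also what makes it immune to recoding. A reader might infer that sinusitis has no check whatever. The documents do not support that: objective 1 and the drug-based rate both count sinusitis prescriptions. What stands is that neither is offered as a check on objective 4, and both are diluted and not tied to t6.

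A second reply is that the incentive is assumed. Table 1 benchmarks each condition once, on previous-year data, and no later report re-scores it. The article describes no reward tied to performance. It says the code is associated with the visit, not who assigns it; that the physician does so is a reasonable inference. This reply stands, so the shift is plausible but not shown.

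A reader might also infer that visits recoded to sinusitis after t3 raise the objective 4 pre-period and so enlarge its later fall. That direction is not established. Table 3 gives 18 pre-months and 6 post-months. Recoding prompted at t3 touches 3 of the 18 and, if it persists, all 6 of the post-months, which would tend to hide a fall. The article also plans t0 as an alternative start for objectives 3 and 4.

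Further, table S1 is not shown. Moves between codes that it already contains would leave objective 3 unchanged. Finally, an analysis plan not shown here may add a sinusitis check. The article itself, however, fixes the outcome, lists its sensitivity analyses and names the coding check for one indication only.

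**Conclusion.** The concern holds as a limit on interpretation with a partial remedy already in the plan. The objective 3 and 4 rates would fall under a coding shift confined to participants, and the controls would not remove it. Objective 3 is the better protected, with a named code-independent analysis. Objective 4 has only indirect cover, and for neither objective is there a described analysis of how many visits carry the target diagnosis.

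The size is illustrative. It rests on assumed baseline rates, on only treated visits moving, and on a 15% threshold that the article set for the all-visit rate. Even 6 visits per 100 at a rate of 30 means relabelling one treated visit in five. The documents do not show that coding would shift that far, or at all. The case for acting is that the ambiguity is foreseeable and cheap to resolve, not that the result is expected to be false.

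**What to change.** Add three sensitivity analyses, using the same controlled model:

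- (a) Prescriptions per 100 visits over one pooled group of acute respiratory diagnoses (the table S1 codes, acute sinusitis and the neighbouring codes to which visits could move), with intervention points at t3 and t6. A treated visit that moves within the group leaves both totals unchanged.
- (b) Visits coded to each target indication as a share of all visits.
- (c) For acute sinusitis at t6, a drug-based rate or a rate with all visits as denominator.

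State that a fall in an indication-specific rate, and any rise in pneumonia diagnoses, will be interpreted alongside (a) and (b). A hard rule that a fall counts only if (b) is stable is not advised. It would need a criterion for stability, the article expects COVID-19 to disrupt primary care, and guidelines may legitimately change diagnosis.

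The cost is plan wording and a few extra model fits. Table 2 already requires visit counts for the target indications, and the Ethics and dissemination section describes data stratified by month and reason for visit; the extract must also hold counts for the neighbouring diagnoses. The pooled rate is less sensitive than the targeted one, so it should support the targeted outcomes and not replace them.

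### Outcomes 3 and 4 use visits for the indication as denominator; the reports may change that count, and no planned outcome would show it, with the main gap at acute sinusitis

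*Protocol article*

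**What the plan says.** Under Outcomes, the monthly rate for each provider is "calculated as the number of prescriptions for a particular indication divided by the number of patient visits for that indication in a month", times 100. Outcome 3 is "The prescribing rate for visits classified as being for a viral respiratory condition" and outcome 4 is "The prescribing rate for acute sinusitis visits". Under Covariates, Table 2 gives the offset as "Number of patient visits for given indication". A visit is assigned to the viral respiratory group "as defined by the primary International Classification of Diseases, Ninth Revision (ICD-9) code associated with the visit" (Intervention). Nothing restricts the denominator to first visits or groups visits into illness episodes.

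Outcomes concedes that prescribing is only a proxy for appropriate prescribing, then takes the view that "any reduction in prescribing as a result of the intervention is likely to be positive".

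Sensitivity analyses contains two safeguards that bear on the point. One is an analysis "using the prescribing rates (for all visits) for antimicrobials most often prescribed for viral respiratory conditions"; its stated reason is possible miscoding of indications, and it is worded for viral respiratory conditions only. The other is a check for negative effects: "the frequency of bacterial pneumonia and pyelonephritis diagnoses and (2) the number of hospital admissions". Admissions can be examined only in Israel, so in Ontario the listed checks are the two diagnoses. The number of visits for an indication is not listed as an outcome anywhere.

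**The concern.** An offset treats its count as exposure that the intervention leaves alone. Here the second and third reports ask physicians to prescribe less at viral respiratory and sinusitis visits, and whether a patient was treated may affect whether that patient comes back. A course given at the first visit scores one prescription per one visit. The same course deferred to a same-code return visit scores one per two. A return visit without a prescription also lowers the rate.

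Concurrent controls do not cancel this, because a changed return pattern would arise only among participants' patients. What is at stake is the size and reading of the effect for objectives 3 and 4: part of a lower rate could reflect more visits rather than fewer courses, and the planned outputs could not separate the two.

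**Working it through.** **Plan's own figure.** The protocol gives no figure on this point. Its one calculation, the sample size, reproduces: (1.645 + 1.282)² × (1/0.126 + 1/0.107) / [ln(0.126/0.107)]² ≈ 5,540 visits per group, and 5,540/368 = 15.05 physicians against about 15 stated. It concerns all visits and does not bear on this issue. Only its 15% reduction is borrowed below.

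**Inputs.** From Sample size: s = 0.15, applied as the share of first-visit prescriptions withheld. Assumed, because the documents give none of them for these indications: p, the share of episodes prescribed for at the first visit (0.3 to 0.7); r, the share of withheld patients who return to the same provider under the same code (0.1 to 0.4); q, the share of those returners then prescribed for (0 to 1).

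**Formulas.**
- Reduction per episode = s(1 − rq).
- Visits per episode rise by the factor 1 + psr.
- Reduction per visit = 1 − [1 − s(1 − rq)] / (1 + psr).

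Worked case, p = 0.5, r = 0.2, q = 0.5: per episode 0.15 × 0.9 = 13.5%; visit factor 1 + 0.5 × 0.15 × 0.2 = 1.015; per visit 1 − 0.865/1.015 = 14.8%. The overstatement is 1.3 points.

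| r, q | Per episode | Per visit, p = 0.3 | p = 0.5 | p = 0.7 |
|---|---|---|---|---|
| 0.1, 0 | 15.0% | 15.4% | 15.6% | 15.9% |
| 0.2, 0.5 | 13.5% | 14.3% | 14.8% | 15.3% |
| 0.4, 1 | 9.0% | 10.6% | 11.7% | 12.7% |

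The overstatement runs from 0.4 points (p = 0.3, r = 0.1) to 3.7 points (p = 0.7, r = 0.4, q = 1). The matching rise in visits for the indication is psr: 0.3 × 0.15 × 0.1 = 0.45% up to 0.7 × 0.15 × 0.4 = 4.2%.

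**Direction.** The table gives treated patients no return visits. Now let 15% of treated patients return as well, with a true 15% reduction per episode and no prescriptions at return visits. Visits per episode are 1 + 0.15p + u(1 − p) before, and the same expression with 0.85p in place of p after, where u is the return share of untreated patients. For p = 0.3 to 0.7:
- u = 0.25 (10 points more often): reads 15.3% to 15.8%.
- u = 0.15 (equally often): reads 15.0%.
- u = 0.05 (10 points less often): reads 14.6% down to 14.2%.

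**Bounding case.** If every withheld patient returns under the same code and is then treated (r = q = 1), use per episode is unchanged. The apparent reduction is 1 − 1/(1 + 0.15p) = 4.3%, 7.0% and 9.5% at p = 0.3, 0.5 and 0.7. A wholly spurious 15% would need 1/0.85 − 1 = 17.6% more visits for the indication.

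**The case against.** The best defence is that a per-visit rate is a coherent choice. The feedback reports benchmark prescribing per 100 visits (Table 1), so the outcome measures the behaviour they target. The drug-based analysis has all visits as denominator: extra same-indication visits are diluted, and a deferred course counts whatever its code. Objective 1 also runs over all visits. At the protocol's 0.126 per visit, the same formula with r = 0.1 to 0.4 gives only about 0.2 to 0.7 points. All of this stands, and it largely settles objective 3. It does not reach objective 4, and it does not make a change in visit counts visible.

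A reader might infer more than the documents support, in three ways.
- That the bias always favours the intervention. It depends on the difference in return rates between untreated and treated patients, which the documents do not give, and it can be zero or reversed.
- That treatment failure is being scored as benefit. The abstract describes the targets as conditions that usually need no antimicrobial, so a return visit is not shown to be failure. A failure recoded to another diagnosis, such as pneumonia, does not enlarge the denominator; its prescription simply leaves the outcome.
- That the trial could report lower prescribing with use unchanged. That is the bounding case, which needs every withheld patient to return to the same provider, under the same code, and be treated. Even then the false reduction at a 15% cut stays below the 15% the protocol calls clinically meaningful.

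**Conclusion.** The point holds in a limited form. Outcomes 3 and 4 rest on a post-intervention count that the intervention may change, and nothing planned would reveal such a change. If untreated patients return more often than treated ones, to the same provider and under the same code, the per-visit reduction exceeds the reduction in use. The excess is about 0.4 to 3.7 points after a 15% first-visit cut; the upper end is roughly a quarter of the target effect. That range rests wholly on assumed baseline rates and return shares, and on no return visits among treated patients. The sign is not established by the documents. The exposed outcome is acute sinusitis, which has no stated all-visits analysis. This is an inexpensive improvement to make; it does not show that the planned outcomes are invalid.

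**What to change.** 1. Fit the same controlled interrupted time-series to the monthly number of visits for viral respiratory conditions and for acute sinusitis, and report the results beside the negative-effect outcomes. The rate and visit results can then be combined: in the worked case a rate ratio of 0.852 times a visit ratio of 1.015 returns 0.865, the true per-episode ratio. Because the plausible rise in visits is small (0.45% to 4.2%), give an estimate with its interval, and do not read a non-significant change as no change.

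2. Repeat objectives 3 and 4 as a sensitivity analysis with all visits as the offset, giving objective 4 priority, and interpret the indication-specific rates alongside both analyses.

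**Cost.** Two further analyses, each fitted for two indications. No new data should be needed: Table 2 already requires visits for each indication, and objective 1 requires all visits. The all-visits rate is less specific and moves with overall visit volume and case mix, including during the pandemic.

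Counting episodes, or using practice size as the offset, would ask for more than the documents show to be available. Ethics and dissemination describes the data as per-visit rates by month and reason for visit, and practice size is not among the Table 2 variables. Neither is needed to close the gap.
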